## Abstract

**Background:**

Early detection of exacerbations by COPD patients initiating prompt interventions has shown to be clinically relevant. Until now, research failed to identify the effectiveness of a written individualized Action Plan (AP) to achieve this.

**Methods/Design:**

The current multicenter, single-blind RCT with a follow-up period of 6 months, evaluates the hypothesis that individualized AP's reduce exacerbation recovery time. Patients are included from regular respiratory nurse clinics and allocated to either usual care or the AP intervention. The AP provides individualized treatment prescriptions (pharmaceutical and non-pharmaceutical) related to a color coded symptom status (reinforcement at 1 and 4 months). Although usually not possible in self-management trials, we ensured blinding of patients, using a modified informed consent procedure in which patients give consent to postponed information. Exacerbations in both study arms are defined using the Anthonisen symptom diary-card algorithm. The Clinical COPD Questionnaire (CCQ) is assessed every 3-days. CCQ-recovery time of an exacerbation is the primary study outcome. Additionally, healthcare utilization, anxiety, depression, treatment delay, and self-efficacy are assessed at baseline and 6 months. We aim at including 245 COPD patients from 7 hospitals and 5 general practices to capture the a-priori sample size of at least 73 exacerbations per study arm.

**Discussion:**

This RCT identifies if an AP is an effective component of self-management in patients with COPD and clearly differentiates from existing studies in its design, outcome measures and generalizability of the results considering that the study is carried out in multiple sites including general practices.

**Trial Registration:**

NCT00879281

## Background

Chronic obstructive pulmonary disease (COPD) is characterized by airflow limitation that is not fully reversible. This airflow limitation is usually progressive and associated with an abnormal response to noxious particles or gases [1]. COPD is a major cause of morbidity and mortality throughout the world[2]. Its stable state is interrupted by periods of worsening symptoms which vary in severity and frequency both during the course of a patient's illness and between patients. Depending on aetiology and severity, these periods may be referred to as exacerbations. Exacerbations are important because of their impact on morbidity and mortality. They may hasten disease progression by accelerating the decline in lung function [3,4] and have a significant effect on quality of life [5,6]. Adjusted for disease severity, patients with exacerbations show higher mortality rates than patients without exacerbations [7,8].

According to international guidelines, exacerbations should be treated with inhaled bronchodilators (particularly inhaled beta2-agonists with or without anticholinergics) and oral corticosteroids. Patients experiencing COPD exacerbations with clinical signs of airway infection (e.g., increased sputum purulence) may benefit from antibiotic treatment [1]. Not all exacerbations are captured by reliance on healthcare contacts. Previous studies have shown that less than 50% of exacerbations will not be reported to the healthcare providers and subsequently do not receive the correct treatment [9-11]. It is debatable whether unreported exacerbations are sufficiently mild that they can be disregarded. More than that, patient recognition of exacerbations and prompt therapy have shown to improve exacerbation outcomes [12]. In addition, patients who refrain from seeking treatment for an exacerbation or have lower self-management capacity show higher hospitalization rates compared to those who seek early treatment from physicians or have better self-management capacity [13]. This underlines the relevance of improving self-management skills to enhance early detection and taking early and appropriate actions by patients in exacerbation episodes.

Until now, little data is available on which methods are effective in enhancing self-management associated with exacerbations. A potential effective method to help patients to recognize and anticipate on the early symptoms of an exacerbation, is an 'action plan' (AP). APs encourage patients to identify daily variations in symptoms and when needed, take the appropriate actions, i.e. change medication regime, or visit a health care provider. Until recently, evidence on effectiveness of using APs is relatively moderate. A systematic Cochrane review including only three randomized controlled trials with relatively small sample size and methodological limitations showed no effects of APs on clinical COPD outcome parameters or healthcare resources [14]. Nevertheless, it was concluded that APs provide an approach to increase patients' exacerbation-related self-management strategies. However, data are still insufficient to draw conclusions in terms of clinical outcomes or healthcare utilization. These findings highlight the need for continued research in this field using high quality randomized controlled trials with adequate sample size.

This present study aims at evaluating the effectiveness of an AP as an addition to care as usual in a randomized controlled trial. We hypothesize that in the event of an exacerbation an AP aiming at early contacting healthcare providers and thus prompt intervention, leads to faster recovery in symptoms and health status in patients with COPD. Secondary outcomes will include self-management behaviour such as contact/treatment delay, self-efficacy and healthcare utilization. This article provides a detailed description of the study background, the targeted population, study methodology and subsequently compares this with previous randomized trials regarding effectiveness of APs in COPD treatment.

## Objectives

### Main objective

To evaluate effectiveness of an individualized Action Plan on health status recovery time (days), in the event of an exacerbation.

### Secondary objectives

To evaluate effectiveness of an individualized Action Plan on in the event of an exacerbation on, symptom recovery time (days), treatment delay, healthcare utilisation, health-related quality of life (HRQL), depression and anxiety and self-efficacy.

## Methods

### Design

The study is conducted as a single-blind randomised controlled trial, with a 6 months follow-up. Patients are randomly assigned to either care as usual or treatment with an individualized AP as an addition to care as usual. The randomisation procedure is performed by a respiratory nurse (RN). To conceal the assignment sequence, a central web-based service on a 1:1 basis is used. Randomisation is stratified by centre and gender.

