### Recruitment and informed consent

Patients are recruited from seven regional hospitals and five general practices in the Netherlands. Inclusion takes place within a period of 5 months (winter - spring). Medical records of patients with a scheduled visit to a respiratory nurse or practice nurse (from here referred to as respiratory nurse) are screened for in- and exclusion criteria by a respiratory or family physician. Eligible candidates receive an information letter about the content of the study two weeks prior to a scheduled (regular) visit to the respiratory nurse (figure 1) including an informed consent form. One week before this visit, patients are contacted by telephone by one of the researchers to get their permission to send a baseline assessment questionnaire and to provide additional information when needed. The informed consent form and baseline questionnaire are turned in at the visit to the respiratory nurse.

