### Sample size

Based on two studies, a median health status recovery time around 12 (IQR 8-16) days is expected [9,27]. Unfortunately we do not know the shape of the underlying distribution. Nevertheless, a nonparametric test might require either more or fewer subjects compared to a Students' t-test, but they never require more than 15% additional subjects if 1) the number of subjects is reasonably high: (how high depends on the nature of the distribution and test, but figure at least a few dozen) and 2) the distribution of the data is not unusual (does not have infinite tails, in which case its standard deviation would be infinitely large)[28].

Hence, we adopted the general rule for computing the sample size required for a t-test. In a normal distribution the distance between the first quartile and the median is approximately 0.67 times the standard deviation of the distribution. Thus, if we assume the distribution of recovery time (median = 12, IQR = 8-16) to be normal, the mean of this distribution will be 12, with standard deviation 6. Sample size is calculated based on the smallest detectable change of one 3-day CCQ unit. Using the aforementioned 15%-rule, would mean a sample size of 63 (two tailed t-test) * 1.15 (+ 15%) = 73 exacerbations are needed in both arms to have an 80% chance of detecting a difference, using a two side alpha = 0.05.

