### Data analysis

SPSS 15.0 for Windows (SPSS, Inc., Chicago, IL) will be used for data analysis. Baseline characteristics are expressed as means and standard deviation or medians and interquartile range. All data will be analysed as intention to treat. Differences in CCQ symptom recovery time between both groups will be evaluated using Mann-Whitney *U *test. Number of exacerbations will be reported as weighted exacerbations rates (total number of exacerbations divided by the total person-time of follow up per group). This approach has shown to produce unbiased estimates of a weighted statistical approach adjusted for asymmetry in follow-up times by accounting for each patient's time spent in the trial [31,32]. Statistical significance of weighted rate ratio's are calculated using a Poisson regression model including an overdispersion parameter to account for variability in exacerbation rates between patients. Other variables will be analyzed using paired student t-test (continuous data), chi-square test (binominal data) and Mann-Whitney *U *test (ordinal data). To determine the magnitude of the treatment effect, Cohen's effect sizes are calculated for continuous variables measuring differences in pre- and post-change.

Confidence intervals of the incremental cost-effectiveness ratio's are tested using nonparametric bootstrapping (Monte - Carlo simulation) drawing 100.000 samples[33].

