***Statistics***				
Follow-up (mths)	6	6	12	12
n		56	102	151
Powered on	Δ exa-rt = 1	Δ SGRQ = 5.7	Δ SGRQ = 4	Δ SGRQ = 4
SSC	245	124	124	160

OC, outpatient clinic; GP, general practice; exa-rt, exacerbation recovery time; SGRQ, St George respiratory questionnaire n, number of patients; SSC, sample size calculation; pt, patient; inv, investigator.

Usually, blinding in self-management or educational interventions is nearly impossible, but the so called 'modified informed consent' procedure, does enable a single-blind RCT and consequently compensates for substantial threats to internal validity. In the field of disease management research this can be regarded innovative in terms of methodology.

In the studies of Wood-Baker et al[34] and McGeoch et al[35], randomization was clustered to prevent cross-contamination of educational messages within a practice. Selection bias in cluster randomized trials may threaten the validity of the results. These studies however did not inflate their sample size to accommodate for this clustering effect [36]. We believe that in this robust study (245 patients) the impact of contamination is regulated by the modified informed consent procedure (patient not knowing that the AP is part of the study objective) and the strict instructions of RN's not to inform control patients about the existence of the AP. The remaining threat of contamination does not weigh against the disadvantage of the huge sample size needed in a clustered trial to compensate for the high inter-cluster variations in both patient (i.e socioecomic differences) and healthcare (i.e. number and content of respiratory nurse consultations) characteristics.

Although all studies used an individualized AP, aimed at early recognition of exacerbations, there are some differences between the interventions. Instead of encouraging self-initiation of antibiotics or oral corticosteroids, the AP used in the current study aims at early contact with a healthcare provider only. The choice to initiate pharmaceutical treatment is left to the physician. Moreover, we have respiratory nurses to evaluate use of the AP and provide additional information when needed. Reinforcement has shown to be essential in changing self-management behaviour, leading to better use of the intervention [37].

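### The primary test leaves out the centre and gender strata used in randomisation, giving up some precision if those strata are prognostic

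*Protocol article*

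**What the plan says.** Design: "a central web-based service on a 1:1 basis is used", and "Randomisation is stratified by centre and gender". Recruitment and informed consent: "Patients are recruited from seven regional hospitals and five general practices in the Netherlands", which makes 12 centres and up to 24 centre-by-gender cells.

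Data analysis: "Differences in CCQ symptom recovery time between both groups will be evaluated using Mann-Whitney" (the U test). This is the only sentence that assigns a test to CCQ recovery time, so I read it as the primary analysis. None of the other methods in that section (Poisson regression, t-test, chi-square, further Mann-Whitney tests) mentions centre or gender.

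The Discussion argues against cluster randomisation by pointing to "the high inter-cluster variations in both patient (i.e socioecomic differences) and healthcare" characteristics. The authors therefore expect centres to differ. They give no intraclass correlation and no gender effect for recovery time.

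**The concern.** Stratified randomisation makes the arms similar within each stratum, so stratum differences contribute less to the chance difference between arms. An unstratified test still counts those differences as noise. If the strata predict recovery time, the null variance is overstated with respect to the strata, and the precision bought by stratifying is not used.

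What is at stake is efficiency. Ignoring the strata does not by itself create false positives.

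**Working it through.** **1. The plan's own sample size.** Inputs from the Sample size section: recovery time taken as normal, averaging 12 days, SD 6 days; a target difference of one CCQ unit, so 3 days; and enough exacerbations "to have an 80% chance of detecting a difference, using a two side alpha = 0.05".

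- Standardised difference: 3/6 = 0.5.
- n per arm = 2(1.96 + 0.84)²/0.5² = 62.7, so 63. Then 63 × 1.15 = 72.45, so 73. The stated figure reproduces.
- The 80% belongs to 63 per arm. With 73, the noncentrality is 0.5 × √(73/2) = 3.02, and t-type power is Φ(3.02 − 1.96) = 85.6%. For a Mann-Whitney test on normal data (relative efficiency 3/π = 0.955), 3.02 × √0.955 = 2.95, and power is Φ(0.99), about 84%.

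**2. Size of the cells.** 146 exacerbations over 24 cells is 146/24 = 6.1 per cell, or about 3 per arm.

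**3. Effect on the plain test's error rate, one episode per patient.** With perfect balance and a stratum share R² of the variance (assumed), the true type I error is 2[1 − Φ(1.96/√(1 − R²))]. That gives 4.4, 3.9 and 3.4% at R² = 5, 10 and 15%. The formula is a limit, because randomisation balances patients, while only about 0.70 × 0.85 = 59.5% of them contribute an episode. A simulation with 24 equal cells, blocks of 4 (assumed) and about 146 episodes gave 5.2, 5.2, 3.5, 3.2 and 3.5% at shares of 0, 5, 10, 20 and 30% (Monte Carlo error about 0.6 points). A second simulation gave about 4.2 to 4.5% at 10 to 15%. The conservatism is real but small, and it is not visible at 5% or below.

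**4. Power with additive adjustment.** Ranks were regressed on arm, centre and gender. Assumptions: 7 hospitals of 26 patients and 5 practices of 12, blocks of 4, about 145 single episodes, outcome in 3-day units, a 3-day effect, and 3,000 runs per cell (Monte Carlo error about 0.7 points).

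| Variance share of strata (assumed) | Plain Mann-Whitney | Adjusted | Change in points |
|---|---|---|---|
| 0% | 80.6% | 79.5% | -1.1 |
| 5% | 82.8% | 81.6% | -1.2 |
| 10% | 82.4% | 83.8% | +1.4 |
| 15% | 82.2% | 85.5% | +3.3 |
| 20% | 83.7% | 87.9% | +4.2 |
| 30% | 84.0% | 90.8% | +6.8 |

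The adjusted type I error was 4.4 to 5.4%. A separate simulation of the same kind gave about -1 at 0%, +0.5 to +3 over 5 to 15%, and about +8 at 30%. Taken together and rounded, the changes at 0, 5, 10, 15 and 30% are roughly -1, 0, +1, +3 and +8 points.

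**5. Power with a rank test stratified over all 24 cells (van Elteren).** Set-up as in step 3, Monte Carlo error about 1.2 points.

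| Variance share (assumed) | Plain | van Elteren |
|---|---|---|
| 0% | 83% | 76% |
| 5% | 84% | 77% |
| 10% | 84% | 81% |
| 20% | 85% | 86% |
| 30% | 83% | 86% |

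Pooling the five practices into one stratum did not rescue this test: van Elteren against plain was 81.5 v 85%, 81 v 83% and 83 v 84% at 5, 10 and 15%.

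**6. Repeat episodes.** The sample size counts exacerbations, and the Exacerbations section lets a patient have a further event after two stable weeks. With an assumed mean of 1.7 episodes per exacerbating patient and a within-patient correlation of 0.2 to 0.4, the plain test's type I error was 6 to 11% at every stratum share tried (0 to 20%).

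**The case against.** The strongest reply is that the premise has no number behind it. The Discussion speaks of variation in patients and care, not in recovery time, and it is silent on gender. Recovery is also judged against each patient's own pre-exacerbation CCQ score, which may remove some of the differences between centres. On this view the loss could be nil. It harms power only, and an adjusted analysis may sit in an analysis plan that is not shown. The first part stands: the size is unknown, and at a 5% share or less adjustment gains nothing. The last part does not remove the point, because the article commits to a named primary test and that test does not follow the stated randomisation.

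A reader might also infer three stronger things, none of which the document supports:

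- **That the test is conservative overall, or its error bars too wide.** Step 6 shows that clustering of episodes within patients can make the net error anti-conservative. No confidence interval is stated for the primary comparison in any case.
- **That power falls below a target with no margin.** The 73 per arm already contains the 15% allowance, and in every simulated setting above the plain test kept more than 80%.
- **That any stratified test would do better.** Step 5 shows the fully stratified one losing power up to a share of about 10%.

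**Conclusion.** The point holds as a modest loss of efficiency. The randomisation factors are stated, the primary test is stated, and they do not match. At assumed variance shares of 10 to 15% the gain forgone is about 1 to 3 points of power. It becomes substantial only if the strata explain far more (about 8 points at 30%), and adjustment costs about 1 point if they explain nothing. These figures assume one episode per patient, a normal recovery time with SD 6 days read in 3-day units, blocks of 4, and the plan's 3-day effect. They say nothing about the net direction of the test's error once patients contribute several episodes.

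**What to change.** Amend the Data analysis section so that the primary comparison adjusts additively for centre and gender. Examples are a rank-based regression or a time-to-recovery model, with centre as a fixed or random effect, the small general practices pooled, and patient-level clustering allowed for. State the pooling rule in advance. Do not use a van Elteren test over all 24 cells. Keep the plain Mann-Whitney test as a sensitivity analysis. Table 1 lists stratification by centre only, so reconcile it with the Design section at the same time.

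The cost is a change of wording, with no new patients or data. The downsides are the need for a pooling rule and about 1 point of power if centre and gender turn out not to be prognostic.

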### Blinding and ethical considerations

Fundamental bias can be introduced in randomized trials if patients cannot be masked for the allocated intervention and subjective outcomes are assessed. For obvious reasons, blinding in behavioural and self-management interventions is usually not possible. However, a modified informed consent procedure enables a single-blind design. In the present study an informed consent to postponed information procedure is used, keeping the patient unaware of the AP being the major study aim. This procedure is used to deal with serious threats to internal validity and justified since the intervention entails no risk. Using a regular full informed consent procedure and by absence of a placebo intervention, patients would be fully aware of the study purpose and treatment allocation. This awareness of patients might lead to biased results, especially because the primary outcome measures of this study are subjective (e.g. HRQoL and symptoms). This postponed informed consent procedure has shown to be a valuable solution to obtain valid assessment of subjective outcomes in a trial in which patients cannot be blinded to the intervention[15,16], also in patients with COPD [17]. In addition, in a Dutch cohort, patients did not have objections to this procedure and did not refuse participation more often[18]. Our modified informed consent procedure implies that all patients are informed about the fact that, besides the outcome assessment aiming at gaining more insight in daily symptom variations, the study has another purpose. Patients are told that they will be informed about this additional research question only after follow-up because informing during recruitment would affect study results. A letter with postponed information about the additional research question, the randomization, allocation and reasons for not informing the patient during recruitment is sent after the collection of all outcome data. Meanwhile, the medical ethical committee of the University Medical Center Utrecht has approved this procedure (08-275). Using the modified informed consent procedure in our trial, we deal with the following threats to internal validity:

#### Selection bias by attrition or dropout

Patients' preference for allocation to the treatment arm and receiving "the innovation" above care as usual might result in increased dropout in the control group, due to being dissatisfied or lack of interest[19].

#### Resentful demoralization/compensatory rivalry

Behaviour of the control group may alter as a result of the study, not due to the independent variable (intervention vs. control). In our study, the control group might be dissatisfied not receiving "the innovation", which increases the risk of biased results. Changes in outcome may only be affected due to a demoralized and perhaps less motivated control group not due to the independent variable. In addition, control patients may compensate by changing their behaviour, which might result in dilution of the intervention effect.

#### Desire to please the investigator/loyalty bias

Patients in the intervention group, who receive "the innovation", might make more favourable follow-up assessments out of loyalty to the programme's staff.

#### Contamination

By knowing that the AP aims at early recognition and action in case of changing symptoms, control patients behaviour might also be influenced by this undesirable knowledge. If subjects in the control group adopt intervention behaviour, a lack of differences between experimental and control groups may be observed (dilution of the effect).

This study has been approved by the Medical Ethical Committee (08-275) of the University Medical Centre Utrecht. Written informed consent is requested from all patients prior to participation in the study.

